### Aims

The central aim of this randomised controlled pilot trial is to examine whether a specifically tailored, brief (10 sessions), computerised CBM training (approach bias modification versus sham) is able to reduce binge-eating episodes in BN and BED patients (primary efficacy endpoint). More precisely, from pre-treatment to 2-month follow-up, BN and BED patients who receive real CBM are expected to report a greater reduction in the number of objective binge-eating episodes during the previous 2 months than those who receive sham CBM.

Additionally, we will investigate whether this CBM programme reduces global eating disorder psychopathology from pretreatment to follow-up, and trait and cue-elicited food craving, food intake and approach and attentional bias towards visual food stimuli in BN and BED patients from pre- to post-treatment. Finally, we will assess treatment acceptance by attrition rates and by means of a specifically designed feedback form. Specifically, as compared to patients in the sham CBM condition, patients in the real CBM condition are expected to show (1) decreased global eating disorder psychopathology from pre-treatment to follow-up, (2) decreased approach and attentional bias towards food cues, (3) decreased state food craving after cue exposure, (4) decreased trait food craving as well as (5) reduced food intake in a bogus taste test from pre- to post-treatment. In an exploratory analysis we will examine the patients’ acceptance of this specific CBM intervention, taking dropout rates and scores on a feedback form into account (treatment acceptance).

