### Sample size

Previous randomised controlled trials comparing real and sham versions of approach bias modification in clinical samples applied a repeated measures ANOVA design (group × time) to examine treatment-specific changes and have reported small-to-medium effect sizes (η_p_^2^ between 0.05 and 0.06) [27, 29, 30]. Using the smallest effect size that has previously been reported, a total sample size of 40 patients will have 80 % power to detect an effect of this size using a 2 × 2 repeated measures ANOVA with a 0.05 two-tailed significance level. The percentage of data lost owing to errors in the applied neuropsychological tasks was 7 % at the maximum in previous studies. Taking this and a potential dropout rate of 25 % into account, a minimum of 53 patients must be included. Thus, we will recruit 27 patients for each group (total *n* = 54).

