#### Post-treatment assessment

The post-treatment assessment will take place after the last training session, and will include the same elements as the baseline assessment except for the Eating Disorders Examination.

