#### Primary outcome measure

▪ Eating Disorder Examination (EDE) [53, 54]: the primary outcome variable in this study is the treatment-specific change from baseline to 2-month follow-up in the number of objective binge-eating episodes as assessed by the EDE. The EDE is a reliable and valid as well as widely used measure of eating disorder symptoms and is regarded as the instrument of choice for the assessment and diagnosis of eating disorders according to the DSM-5.

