### Analyses

To determine quality, completeness and variability of the outcome measures, descriptive statistical analyses and graphical methods will be used. To evaluate treatment-specific changes over time in patients, a 2 × 2 repeated measures ANOVA, with group as between-subject factor and time as within-subject factor, will be applied. The size of the treatment effect on the outcome measure (EDE) will be the difference in outcome data between those in the two treatment conditions at follow-up. Additionally, multiple regression models will permit exploration of the relationship between changes in the cognitive measures and symptom improvement. No interim analyses are planned. A two-tailed significance level of *p* < .05 will be used throughout. Both completer and intent-to-treat analyses will be performed. Missing values will be replaced by using the Last Observation Carried Forward (LOCF) method for the intent-to-treat analysis. As this is a pilot trial resources do not stretch to setting up a Monitoring Committee. Analyses will be conducted by the principal investigators. As CBM is a safe procedure with no known side effects we do not expect any unexpected adverse reactions, serious or unexpected serious adverse reactions. We will report any adverse reactions and serious adverse events. It is intended that the results of the study will be reported and disseminated by the principal investigators at international conferences and in peer-reviewed scientific journals.

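### The primary test concerns change from baseline, but the declared treatment effect is the difference at follow-up; one baseline-adjusted contrast should supply the p-value, the estimate and the confidence interval

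*Protocol article*

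**What the plan says.** Three places in the protocol article agree on change from baseline:

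- Aims: patients given real CBM "are expected to report a greater reduction in the number of objective binge-eating episodes during the previous 2 months" than those given sham.
- Primary outcome measure: "the primary outcome variable in this study is the treatment-specific change from baseline to 2-month follow-up", counted with the EDE.
- Analyses: "a 2 × 2 repeated measures ANOVA, with group as between-subject factor and time as within-subject factor, will be applied".

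The next sentence of Analyses departs from this. The size of the treatment effect on the EDE "will be the difference in outcome data between those in the two treatment conditions at follow-up". It mentions no baseline value, and no baseline-adjusted analysis is stated anywhere in the article.

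The EDE is given only at baseline and at the 2-month follow-up, because the post-treatment visit "will include the same elements as the baseline assessment except for the Eating Disorders Examination". Baseline assessment is completed before allocation (Baseline assessment). Randomisation is stratified for BN and BED only (Randomisation).

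**The concern.** With two EDE timepoints, the group × time test is the two-sample t-test on change scores (F = t²). The p-value therefore belongs to the difference in change, while the declared effect is the difference at follow-up. One endpoint has two estimators, and the text does not say which governs.

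Baseline binge frequency is not a stratification factor and the trial is small, so a chance imbalance in the count is to be expected. The follow-up difference carries all of that imbalance, whereas the change score subtracts it. A reader could be shown a significant p-value beside an effect whose confidence interval spans zero, or the reverse. Neither contrast makes the best use of a baseline count that is collected before allocation.

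**Working it through.** **Inputs.** From Sample size: partial η² = 0.05, 40 analysable patients, 54 recruited (27 per arm). From Analyses: two-sided 0.05. The correlation ρ between baseline and follow-up counts is not stated. I assume 0.5 and show a range. I also assume equal SDs at both times and a linear, roughly normal outcome.

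**1. The plan's own figure.** The protocol says "a total sample size of 40 patients will have 80 % power to detect an effect of this size". For the 2 × 2 interaction, f² = 0.05/0.95 = 0.0526 and λ = f² × N × 2/(1 − ρ), with 1 and 38 df. At ρ = 0.5, λ = 0.0526 × 40 × 2/0.5 = 8.42 and power is 80.7%, which reproduces the stated 80%. At other values of ρ power is 51.6% (ρ = 0), 66.6% (0.3) and 95.4% (0.7). So 0.5 is the value that matches the text.

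**2. The implied effect.** For a mean difference d in outcome SDs, the change-score test has λ = (N/4)d²/[2(1 − ρ)]. At ρ = 0.5 this is 10d² = 8.42, so d = 0.918 SD.

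**3. The gap between the two contrasts.** Difference in change = follow-up difference − baseline difference. The baseline difference has mean zero and SD √(2/n):

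- n = 27 per arm: √(2/27) = 0.27 SD, 95% range ±1.96 × 0.272 = ±0.53.
- n = 20 per arm: √(2/20) = 0.32 SD, 95% range ±1.96 × 0.316 = ±0.62.

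Relative to 0.918 SD, the SD of the gap is 0.272/0.918 = 0.30 and 0.316/0.918 = 0.34, or about a third.

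**4. What a reader would see.** Simulated normal trials, 20 per arm, ρ = 0.5:

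| True effect | Mean of change, follow-up and adjusted estimates | Exactly one of the two 95% CIs (change, follow-up) excludes zero | ANOVA significant, but CI of follow-up difference includes zero (share of significant trials) | Opposite signs |
|---|---|---|---|---|
| 0.918 SD | all about 0.917 | 22% | 14% | 0.3% |
| 0.459 SD | all about 0.459 | 28% | 49% | 10% |

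**5. Precision.** Per-patient variance in units of the outcome variance is 2(1 − ρ) for change, 1 for follow-up and 1 − ρ² for ANCOVA:

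| ρ | Change | Follow-up | ANCOVA | ANCOVA / better of the two | Power at N = 40, d = 0.918 (change / follow-up / ANCOVA) |
|---|---|---|---|---|---|
| 0.3 | 1.40 | 1 | 0.91 | 0.91 | 66.6 / 80.7 / 83.2% |
| 0.5 | 1.00 | 1 | 0.75 | 0.75 | 80.7 / 80.7 / 89.6% |
| 0.7 | 0.60 | 1 | 0.51 | 0.85 | 95.4 / 80.7 / 97.4% |

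The power figures include the cost of estimating the slope: a variance factor (N − 3)/(N − 4) = 37/36 and one df fewer. At ρ = 0.5 the factor turns 0.75 into 0.77. Because of that cost, at N = 40 the gain vanishes below ρ of about 0.17 (against follow-up) and above about 0.95 (against change).

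**The case against.** **Is the mismatch certain?** The protocol does not call the follow-up difference raw or unadjusted. Since the primary outcome variable is itself defined as a change, the outcome data at follow-up could be read as change scores. That reading is possible but strained. The sentence contrasts the arms at one timepoint and names no baseline, straight after a sentence about change over time.

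**Is anything biased?** No. Both contrasts have the same expectation under randomisation, and the group × time test is valid. It is also the test for which the trial was sized. A reader might infer that the two contrasts target different effects, or that type I error is inflated. The documents support neither.

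**Can two tests disagree?** Only the ANOVA is a planned test. The 22% is not a rate of conflicting planned tests. It is how often the interval around the declared effect would point the other way from the ANOVA. That part of the concern stands, as a matter of reporting.

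**Is the gap as large as the effect sought?** A reader might set the ±0.53 to ±0.62 SD range against 0.46 SD, which is what partial η² = 0.05 means if it is the interaction effect as conventionally reported (2f = 2 × 0.229). But that compares a 95% extreme with an effect for which 40 patients give only about 29% power, so it is not the effect behind the stated 80%. Against 0.92 SD the typical gap is a third.

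**Is the precision gain assured?** Not without ρ, which the documents do not give. A claim that 54 patients would do the work of 72 (54/0.75) needs ρ = 0.5, no dropout and a free slope estimate, whereas the protocol itself allows for 25% dropout. Episodes are also counts, so the exact gains may differ.

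**Conclusion.** The inconsistency stands: the tested contrast is change and the declared effect is the follow-up difference. Its size is that of the chance baseline imbalance, an SD of 0.27 to 0.32 outcome SD, or about a third of the effect that the stated sample size implies at ρ = 0.5. That is enough for the reported effect and its interval to disagree visibly with the p-value. Reversal of sign is rare at that effect and becomes appreciable (about 10%) only at half of it.

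This should be fixed, but it does not invalidate the primary test. The mismatch and the √(2/n) gap do not depend on ρ. The simulation rates and precision gains rest on an assumed ρ, equal SDs and a linear, roughly normal outcome. For ρ between roughly 0.2 and 0.9 the baseline-adjusted analysis is at least somewhat more precise than either stated contrast.

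**What to change.** In Analyses, name one primary contrast: the between-arm difference in objective binge-eating episodes at the 2-month follow-up, from an ANCOVA with the baseline count and the BN/BED stratum as covariates. Take the p-value, the estimate and the 95% CI from that one model. Keep any count model as a sensitivity analysis, since a rate ratio offered as an alternative primary measure would reopen the choice. Align the sentences in Primary outcome measure and Sample size with this contrast.

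If the sponsor prefers to keep the ANOVA, the minimum repair is to define the treatment effect as the difference in change with its 95% CI. That removes the inconsistency but forgoes the precision.

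The ANCOVA costs one or two degrees of freedom and needs no new data, because the EDE count and the diagnosis are both recorded before allocation. Recruitment and data collection have begun, so the change should be made and dated before any unblinded analysis.

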#### Baseline assessment

Binge-eating frequency and general eating disorder symptomatology will be assessed in terms of a specific, structured clinical interview, i.e. the Eating Disorders Examination [53, 54]. Participants will also be weighed and asked to complete a battery of questionnaires relating to eating disorder symptomatology, food craving, depression and anxiety, as well as neuropsychological computer tasks that assess approach bias and attentional bias towards visual food cues and working memory. Furthermore, state levels of food craving after cue exposure and food intake will be assessed in laboratory tasks.

Once the baseline assessment is completed, participants will be randomly allocated to the treatment (real CBM) or control (sham CBM) group. Randomisation will be performed independently from the trial team by a central study office at Heidelberg University Hospital. The first CBM session will start on the day of the baseline assessment. Participants in the sham group will be offered the opportunity to receive real CBM after the end of follow-up.

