#### Two-month follow-up

Two months after the post-treatment assessment a follow-up session will be conducted which will involve the Eating Disorders Examination. Finally, the success of blinding will be evaluated by asking participants to guess the treatment allocation. Participants will be unmasked and individuals in the control group will then be offered the real treatment.

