## Discussion

The ABBA study aims to examine the potential of a novel, computerised, short-term treatment module for patients with bulimic eating disorders that targets a specific cognitive bias in the processing of visual food cues, i.e. automatic approach tendencies towards highly palatable food. This is the first study examining this treatment approach in a clinical sample of patients with BN and BED. Particularly in view of the high attrition and relapse rates in bulimic eating disorders, novel treatment approaches are urgently needed [4, 65]. Strengths of the presented study include a rigorous, double-blind, randomised controlled design including a strong control condition with a similar task and equal dosage, and the assessment of potential action mechanisms. Several potential practical and operational issues, however, may pose challenges to the successful and timely completion of the study, particularly regarding recruitment and attrition. Patients with eating disorders are often ambivalent about treatment, which is reflected in high attrition rates and this may become particularly difficult if a participant believes that they are receiving sham treatment, or if the treatment and assessments are experienced as too burdensome.

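### The EDE is taken only at baseline and 2-month follow-up, so the LOCF rule carries baseline forward and gives zero change to every patient without a follow-up EDE

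*Protocol article*

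**What the plan says.** All references are to the protocol article.

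- **Primary outcome measure:** the "treatment-specific change from baseline to 2-month follow-up in the number of objective binge-eating episodes as assessed by the EDE".
- **Baseline assessment (t1):** "Binge-eating frequency and general eating disorder symptomatology will be assessed in terms of a specific, structured clinical interview, i.e. the Eating Disorders Examination".
- **Post-treatment assessment (t2):** this visit "will include the same elements as the baseline assessment except for the Eating Disorders Examination".
- **Two-month follow-up (t3):** "Two months after the post-treatment assessment a follow-up session will be conducted which will involve the Eating Disorders Examination". Table 1 agrees, marking the clinical interview at t1 and t3 only. It marks questionnaires, computer tasks and the Taste Test at t1 and t2 only.
- **Analyses:** a 2 × 2 repeated measures ANOVA (group by time). Two analysis sets are planned: "Both completer and intent-to-treat analyses will be performed". The rule for gaps in the data is then: "Missing values will be replaced by using the Last Observation Carried Forward (LOCF) method for the intent-to-treat analysis". No other method for missing values is given.
- **Sample size:** the calculation takes "a potential dropout rate of 25 % into account".
- **Discussion:** on attrition, "this may become particularly difficult if a participant believes that they are receiving sham treatment".

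**The concern.** LOCF is usually pictured as carrying forward a late on-study value. Here there is none for the EDE, so the rule amounts to an assumption that a patient who misses t3 did not change at all. The ANOVA then treats that zero as a measurement. The EDE global psychopathology score is affected in the same way. So are the secondary outcomes measured only at t1 and t2.

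Two things are at stake. If dropout is equal between arms, a real effect is diluted. If dropout differs between arms and patients improve on average in both, the rule creates a difference where none exists. Under LOCF the intent-to-treat result for the primary endpoint then depends partly on who returned for follow-up.

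**Working it through.** **1. The plan's own figure.** Inputs from Sample size: partial η² = 0.05, N = 40, two-sided 0.05, two time points. The article gives no correlation between time points; ρ = 0.5 is assumed.

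- f² = 0.05/0.95 = 0.0526, so f = 0.229.
- λ = N·f²·m/(1 − ρ) = 40 × 0.0526 × 2/0.5 = 8.42, with 1 and 38 degrees of freedom.
- Power is 80.7 %, so the stated 80 % reproduces. Adding 25 % and 7 % gives 40 × 1.32 = 52.8, the stated 53.
- At ρ = 0.5 the planned effect equals 4f = 0.92 SD of the change score.

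**2. What LOCF does.** A missing t3 EDE takes the t1 value, so change = 0. Let μ be the mean improvement and d the proportion without a t3 EDE. The expected difference in change is

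μ_real(1 − d_real) − μ_sham(1 − d_sham).

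If the 25 % allowance were fully used, 54 × 0.25 = 13.5, so about 13 patients would enter with zero change.

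**3. Equal dropout, 25 % per arm.** The expected difference is 0.75 × (μ_real − μ_sham), a 25 % attenuation, provided dropouts would have responded like completers. The planned 0.92 SD becomes 0.69 SD.

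Power also depends on how much the sham arm improves. The variance of a change score after LOCF is (1 − d)σ² + d(1 − d)μ², which grows with μ. Assume σ = 8 episodes, 27 per arm and a true difference of 4, so that LOCF estimates 3:

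| Sham improvement | Variance real / sham | SE of difference | Estimate/SE | LOCF power (simulated) |
|---|---|---|---|---|
| 0 | 51 / 48 | √(99/27) = 1.91 | 1.57 | 34 % |
| 4 | 60 / 51 | √(111/27) = 2.03 | 1.48 | 30 % |
| 8 | 75 / 60 | √(135/27) = 2.24 | 1.34 | 26 % |

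Completer power is about 34 % in every row. For the planned 0.92 SD, LOCF power is 79 %, 72 % and 63 % when sham improves by 0, 0.5 and 1.0 SD, against about 80 to 81 % for completers.

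**4. No true effect, unequal dropout.** With a common improvement μ, the bias is μ(d_sham − d_real). At μ = 8 it is 8 × 0.10 = 0.8 episodes for 30/20, 8 × 0.20 = 1.6 for 35/15 and 8 × 0.30 = 2.4 for 40/10. Simulated two-sided type I error of the LOCF analysis (t-test on change, which is the group by time test; normal change scores, SD 8, 27 per arm, dropout unrelated to outcome):

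| Dropout sham / real | Improvement 0 | 4 | 8 episodes |
|---|---|---|---|
| 25 / 25 | 5 % | 5 % | 5 % |
| 30 / 20 | 5 % | about 5 % | 6.7 % |
| 35 / 15 | 5 % | 7 % | 12 % |
| 40 / 10 | 5 % | 10 % | 21 % |
| 15 / 35 | 5 % | 7 % | 12 % |

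In the 30/20, 35/15 and 40/10 rows the excess favours real CBM. In the last row the bias has the opposite sign and works against it.

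**The case against.** Several points on the other side stand and limit the finding.

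- **Who is affected.** A reader might infer that every dropout gets zero change. Only patients without a t3 EDE do. The Intervention section lets patients stop treatment, and nothing says they are then not followed up. The 25 % is a planning allowance, and all participants in the authors' proof-of-concept study (a subthreshold sample) completed the training.
- **Power.** LOCF need not cost power. If the sham arm does not improve, power equals that of completers. The estimate is still too small.
- **False benefit.** A reader might infer from the Discussion that sham patients are expected to drop out more. It says only that attrition may be harder if a participant believes they are on sham, and it also names the burden of treatment and assessments. Belief is not allocation: participants are blinded, sham is the same task at the same dosage, and patients on real CBM may also believe they are on sham. The higher error rates need both a wide dropout gap and a large common improvement.
- **Two primary tests.** A reader might infer two primary p-values. The article ranks neither analysis, and a condensed article may leave that to the analysis plan. With equal dropout and an improvement of 8 episodes, the chance that either test is significant under the null is about 7 %.
- **The completer check.** The planned completer analysis is a partial safeguard. It held close to 5 % in these simulations, but they assume that dropout is unrelated to outcome.
- **Pilot status.** The trial calls itself a pilot, which lowers the severity. It also states a superiority hypothesis on this endpoint, so the estimate still matters.

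None of this changes the fact that the stated rule is baseline carried forward.

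**Conclusion.** The point holds, as a should-fix. That LOCF here means baseline carried forward follows from the visit schedule alone and needs no assumption. The 25 % attenuation rests on the planning allowance being used equally in both arms and on dropouts responding like completers. The type I error range, from about 5 % to about 21 %, rests on assumed values for the SD of change, the common improvement and arm-specific dropout, none of which the article gives. The documents support saying that LOCF can bias the primary intent-to-treat result in either direction. They do not support saying that it will produce a false benefit.

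**What to change.** Replace the LOCF sentence in Analyses with text on these lines: *The main intent-to-treat analysis includes all randomised patients and handles missing follow-up EDE data under a missing-at-random assumption, by a likelihood-based model or by multiple imputation. The imputation model contains arm, baseline binge count, diagnosis, site and one or two prespecified t2 scores where available. LOCF, which here is baseline carried forward, and the completer analysis are sensitivity analyses. Secondary outcomes measured at t1 and t2 are analysed under missing-at-random with baseline adjustment.*

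The imputation model should stay small because only about 20 completers per arm are expected at 25 % dropout (27 × 0.75 = 20.25).

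The cost is changed wording and slightly more analysis work with standard software; no new data are needed. Two limits remain. Patients lost before t2 contribute baseline data only. Missing-at-random is itself an assumption, and would fail if dropout followed an unrecorded belief about allocation; the sensitivity analyses are there to probe it.

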In a proof-of-concept study [39] we recently evaluated the efficacy of such an approach bias modification training in a sample of people with high levels of food craving and subthreshold bulimic symptoms. Both the targeted approach bias towards food cues and also attentional bias towards food, trait and cue-elicited food craving, as well as more general eating disorder symptoms, were significantly reduced during the training with medium to large effect sizes in this study. The initial approach bias towards visual food cues was not only reduced (as hypothesised) but actually turned into an avoidance bias. Furthermore, all participants completed the intervention and the majority of them perceived the training as effective in altering daily eating habits. Taken together, these highly promising findings suggested that retraining automatic action tendencies in people with bulimic symptoms by means of computerised CBM may be an effective, feasible and acceptable way of reducing cognitive biases, food craving and binge eating. Thus, a randomised controlled trial with BN and BED patients appeared to be the logical next step.

According to the emotional distress hypothesis of binge eating, cognitive biases constitute latent vulnerability factors that become evident when the individual is confronted with a stressor [40]. Consequently, CBM should be most effective in its impact on cognitive biases and subsequent eating behaviour upon exposure to stressful situations. In fact, it has been demonstrated that CBM attenuates the effects of stressors on symptoms of depression and anxiety [41, 42]. Furthermore, there is a common theoretical basis and strong empirical evidence that negative affect (in response to a stressor) is a key trigger of attentional bias towards food and of binge eating [43–46]. Therefore, we applied a vulnerability-stress model for our CBM programme by using stimuli that induce moderate levels of negative affect before cognitive bias training and assessment.

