### Intervention

Patients in the real CBM condition will conduct a treatment version of the Food Approach-Avoidance Task (Food-AAT) [39]. In this task, participants are shown colour photographs of food and control (i.e. neutral household and office) items on a computer screen. They are required to pull or push a joystick in response to the outline of the picture (round versus rectangular), irrespective of picture content. Format movement assignments are counterbalanced among participants (i.e. half will push round pictures and half will push rectangular pictures). When the joystick is pulled, the picture grows bigger and when it is pushed it grows smaller. This zooming-in and zooming-out emphasises respective sensations of approaching and avoiding and thus combines the proprioceptive (arm movement) and exteroceptive (zooming feature) cues of approach and avoidance behaviour [47]. The treatment version of the Food-AAT adopts an implicit learning paradigm by presenting all food pictures in the ‘push’ (i.e. avoid) format so that participants learn to link avoidance movements to visual cues of high-calorie food. Patients will receive ten 15-min sessions of training over a 4-week period.

Patients in the control condition (sham CBM) will receive the same dosage of the same task but will *not* be trained to avoid food cues in the Food-AAT. Instead, patients in the control condition receive 10 additional sessions of the pre- and post-treatment assessment version of the task (Food-AAT), which requires an equal number of approach and avoidance movements to both food and non-food pictures. Sham (placebo) CBM with an equal dosage, frequency and character was chosen as the comparator treatment in order to examine the specific effects of this form of CBM.

Sessions will take place in dedicated research facilities. In line with the vulnerability-stress model of cognitive biases described in the introduction [48], participants will be presented with a set of pictures that are considered to induce mild levels of negative mood at the beginning of every training session (60 images; duration: approximately 1 min) [49].

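### The stated safety reporting omits non-serious events that nobody attributes to the procedures, which could include a rise in binge eating or distress during the four treatment weeks

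*Protocol article*

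**What the plan says.** The reporting rule is in Analyses: "We will report any adverse reactions and serious adverse events". The sentence before it gives the expectation behind the rule: "As CBM is a safe procedure with no known side effects we do not expect any unexpected adverse reactions".

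The Intervention section describes pictures "considered to induce mild levels of negative mood at the beginning of every training session", with no restriction to one arm. The Background states that "negative affect (in response to a stressor) is a key trigger of attentional bias towards food and of binge eating".

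The post-treatment visit (t2) repeats the baseline elements "except for the Eating Disorders Examination". The EDE returns only at the follow-up visit (t3), two months after t2. Under Aims, the primary endpoint counts objective binge-eating episodes over the preceding two months.

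**The concern.** Under this rule a non-serious event reaches the report only if someone judges it to be a reaction. That judgement is made within a plan that expects no side effects, and in patients whose disorder already consists of binge eating. The event that the protocol's own model predicts, more binge eating after induced negative mood, is therefore the one most easily read as the underlying illness and left out.

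At stake is what the trial can say about harm. The Discussion presents it as the first study of this approach in a clinical sample of patients with bulimia nervosa or binge eating disorder. A report of few or no adverse reactions would not show that binge eating or distress did not rise while patients were being trained.

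**Working it through.** The article gives no figure for this point, so the check compares the reporting scope with the assessment windows.

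**1. What the reporting rule covers (Analyses)**
- Serious event, related or not: reported.
- Non-serious event judged to be a reaction: reported, because the text sets no seriousness limit on reactions.
- Non-serious event not judged to be a reaction: not named.

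**2. Whether events in the third group are plausible on the protocol's own terms**
- Exposure: 10 sessions per patient and 54 patients, so up to 10 × 54 = 540 inductions. This counts exposures and does not estimate harm.
- Mechanism: the Background links negative affect to binge eating.
- Strength: the Intervention section says the pictures "induce mild levels of negative mood at the beginning of every training session", whereas the Background speaks of "using stimuli that induce moderate levels of negative affect before cognitive bias training and assessment". Mild and moderate are different descriptions of the same exposure, and the two sections must be reconciled.

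**3. Whether the EDE sees the treatment weeks**

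Inputs: treatment lasts 4 weeks (Design); the first session is on the day of the baseline assessment (Baseline assessment); t3 is two months after t2 (Two-month follow-up); the look-back is two months (Aims). Assumptions: two months is 61 days, and t2 falls on day 28.
- Baseline EDE window: day −61 to day 0.
- Treatment: day 0 to day 28.
- t3: day 28 + 61 = 89. Follow-up EDE window: day 89 − 61 = 28 to day 89.
- Overlap of the follow-up window with treatment: max(0, 28 − 28) = 0 days.

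All 28 treatment days lie between the two windows. A t2 visit some days after the last session would widen the gap. A t3 visit held early would create a small overlap, equal to the number of days by which it is early.

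**4. What else is collected**
- Questionnaires on eating disorder symptoms, craving, depression and anxiety at t1 and t2 (Baseline assessment, Post-treatment assessment, Table 1). The depression and anxiety scales are listed as screening measures, not as outcomes. Patients who leave before t2 do not supply the second value.
- A researcher present at every session (Intervention), for the stated purpose of adherence.
- Reasons for withdrawal (Screening), which cover only those who leave.
- In the intent-to-treat analysis, last observation carried forward has only the baseline EDE to carry. A patient who worsens and drops out therefore enters as unchanged.

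**The case against.** The strongest reply is that the article states what will be reported, not what is collected. How events are elicited, and how relatedness is judged, may stand in the full protocol, which is not shown. That is right, and no fault is found with the absence of those details. The point rests only on the scope that the article does state.

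A second reply is that the trial already gathers relevant data: the t2 questionnaires, the researcher's presence, documented withdrawals and other treatments, and an acceptance analysis using dropout and a feedback form. This stands in part. These data may show lasting distress, but they are not set up as harm reporting and may miss a temporary rise.

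Some stronger readings are tempting but not supported:
- A reader might infer that all non-serious harm goes unreported. It does not, because any adverse reaction is to be reported.
- A reader might infer that tolerability cannot be compared between arms. The planned acceptance analysis allows some comparison.
- A reader might expect a table by arm to reveal harm from the mood induction. Both arms appear to receive it, so a difference between arms would speak to the retraining only.
- A reader might cite the upper 95% bound with no events in 27 patients, 1 − 0.05^(1/27) = 10.5%. It is correct, but it holds for any arm of 27 under any reporting rule and does not measure this gap.
- The article explains that "resources do not stretch to setting up a Monitoring Committee". That is a matter of resources and is not part of this point.

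**Conclusion.** The point holds in a narrow form. The stated scope leaves out non-serious events not attributed to the procedures. The protocol's rationale makes one such event plausible, and neither EDE assessment covers the 28 days in which it would occur. The t2 questionnaires mitigate this only partly.

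The documents do not show that such harm occurs, and its size cannot be estimated from them. No stated number is wrong and the primary comparison is not biased by the reporting rule. The conclusion assumes that visits keep roughly to the stated schedule and that both arms receive the mood induction, as the Intervention section implies. It is a cheap improvement and does not call the design into question.

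**What to change.** In Analyses, replace the reporting sentence with a commitment to record and report all adverse events in both arms, whether or not judged related.
- Elicit them with one neutral open question, asked by the researcher already present at training sessions, and again at t2 and t3. At t3, ask before participants learn their allocation.
- Do not ask specifically about binge eating at each session. Repeated prompting could alter the behaviour that forms the primary outcome. If a patient volunteers a worsening, record it like any other event.
- Tabulate events by arm and overall. The overall column is needed because both arms appear to receive the induction.
- Describe the change from t1 to t2 in the depression, anxiety and eating-symptom questionnaires already collected, by arm and overall.
- Limit the safety statement to the evidence at hand. For this training, the article's own evidence is a proof-of-concept study in people with high food craving and subthreshold symptoms.
- Reconcile the two descriptions of the strength of the induced mood.

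The cost is one question per visit, one table and a little more data entry. Trial status says recruitment has begun, so the data will be incomplete for participants already enrolled. Randomisation, blinding and the primary endpoint are untouched.
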